Residents who sign the informed consent will participate in the research study starting in January 2011. The research study will consist of 2 phases. In the first phase, half of the study subjects will be randomized to wearing an activity monitor with feedback, and half will be randomized to wearing an activity monitor with no feedback (blinded/control group). This phase will last for 6 weeks. Immediately following the randomized phase, all subjects will be unblinded and wear the activity monitor with feedback. The second phase will be a team competition between the 3 classes of residents (interns, juniors, and seniors). The teams will compete on average number of steps per week for each team. The team competition will last for 6 weeks.

Randomization: Study participants will be randomized in late December to either the intervention arm (activity monitor with feedback) or the control arm (activity monitor with no feedback). The randomization will be stratified by class year (intern, junior, senior).

Parameters to be measured:

The parameters that will be measured for all Be Fit program participants at baseline and at the end of the program are listed in the table below. The survey will collect data on health habits, including smoking, nutrition, physical activity, and sleep.

|  | Baseline  (July-November 2010) | End of program  (May 2011) |
| --- | --- | --- |
| **Physical assessment:** Blood pressure and heart rate, weight, BMI, body fat, waist circumference | X | X |
| **Blood draw:** Fasting lipids | X | X |
| Survey (completed by participant) | X | X |

For those Be Fit participants who enroll in the research study, we will collect data measured by the activity device worn from January through May 2011. The activity device records data on number of steps per day, number of calories burned per day, number of hours slept per night, and number of times awakened per night.

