Data from Fitbit website: Only residents who enroll in the research study will be given a Fitbit activity device. All activity data and sleep data recorded during the study period will be collected. The Fitbit website provides individual data on the number of steps per day, the number of calories burned per day, and the number of hours slept per 24 hour period. This data will be collected from all study subjects during both the randomized phase and the team competition phase of the study.

Study endpoints:

Primary endpoint: The primary endpoint of the study will be average activity level per resident as measured by number of steps per day. In the randomized phase, the average number of steps per day in the intervention group (Fitbit + feedback) will be compared to the average number of steps per day in the control group (Fitbit without feedback). In the second phase, we will compare the change in the average number of steps for each participant compared to their own baseline number of steps from the first phase.

Secondary endpoints: Secondary endpoints will be change in weight during the study period and number of hours of sleep per 24 hour period for each resident. Survey data will be used to examine reported changes in physical activity levels, nutritional habits, and sleep habits. The survey data will also provide data from the SOS-10 scale on change in psychological stress.

Statistical methods:

In the randomized phase, the average number of steps per day in the intervention group (Fitbit + feedback) will be compared to the average number of steps per day in the control group (Fitbit without feedback) using a two-sample t test or a Wilcoxon rank sum test whichever is more appropriate. To determine whether team competition increases activity level, the primary and secondary endpoints from the second phase will be compared to results from the first phase using paired t-tests. The changes in primary and secondary endpoints during study periods will be compared between the two randomization groups using a two-sample t test, and compared among the residency year groups using an analysis of variance approach. To determine if the average hours of sleep per week is associated with changes during study period, Pearson or Spearman correlation coefficients will be used to summarize the correlation between sleep time and change in weight/number of steps.

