Power analysis: For the randomization phase, a sample size of 50 in each group will have 84% power to detect a difference in means of 1200 steps assuming that the common standard deviation is 2000 steps using a two group t-test with a 0.05 two-sided significance level.

For studies involving treatment or diagnosis, provide information about standard of care at Partners (e.g., BWH, MGH) and indicate how the study procedures differ from standard care. Provide information on available alternative treatments, procedures, or methods of diagnosis.

This study does not involve treatment or diagnosis of a medical condition or illness.

Describe how risks to subjects are minimized, for example, by using procedures which are consistent with sound research design and which do not unnecessarily expose subjects to risk or by using procedures already being performed on the subject for diagnostic or treatment purposes.

The risk associated with this research is minimal. The principle investigator oversees all study staff to ensure that procedures are followed which are consistent with sound research design and do not expose subjects to unnecessary risk. The study does not offer a diagnosis or treatment to subjects. The procedures in study were developed using standard nutrition and fitness guidelines and recommendations.

Describe explicitly the methods for ensuring the safety of subjects. Provide objective criteria for removing a subject from the study, for example, objective criteria for worsening disease/lack of improvement and/or unacceptable adverse events. The inclusion of objective drop criteria is especially important in studies designed with placebo control groups.

Subjects will be withdrawn from the study if they leave their employment at MGH or if they request to be removed from the study.

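### Randomization is stratified by class year but the primary arm comparison is unstratified; if class year predicts steps, the planned t test is conservative and gives up power

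*Protocol*

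**What the plan says.** All the relevant text is in the Protocol, Research Design and Methods.

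- **Randomization:** "The randomization will be stratified by class year (intern, junior, senior"). Allocation is equal: "half of the study subjects will be randomized to wearing an activity monitor with feedback", and the other half gets a monitor without feedback.
- **Primary endpoint (Study endpoints):** "The primary endpoint of the study will be average activity level per resident as measured by number of steps per day".
- **Primary comparison (Statistical methods):** in the randomized phase the arms are compared "using a two-sample t test or a Wilcoxon rank sum test whichever is more appropriate". Neither test carries a class-year term. Class year appears in that paragraph only in a separate analysis of variance that compares changes among residency years.
- **Power analysis:** "a sample size of 50 in each group will have 84% power to detect a difference in means of 1200 steps". The calculation takes an SD of 2000 in both arms and a t test at the two-sided 5% level. The text does not say whether 2000 is the SD across all residents or the SD within a class year.

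**The concern.** Stratifying by class year gives the two arms nearly the same mix of interns, juniors and seniors. Differences in step counts between classes therefore largely cancel out of the arm difference. An ordinary two-sample t test does not know this. Its pooled SD still contains the between-class spread, so its standard error describes a less precise design than the one actually run. If class year is related to steps, the confidence interval is wider than it need be, the true type I error is below the nominal 5%, and power is lost.

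A second, separate point concerns the alternative test. The endpoint and the power analysis are framed as a difference in mean steps. The Wilcoxon rank sum test does not estimate that quantity, so a primary result based on it would not address the 1200-step difference for which the trial is sized.

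**Working it through.** **Inputs from the protocol:** n = 50 per arm, difference 1200, SD 2000, two-sided alpha 0.05, equal allocation, stratification by class year.

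**Assumptions, not in the protocol:** R2, the share of within-arm variance in steps that lies between class years, taken from 0 to 0.20; normal data; arms exactly balanced within each class.

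**Step 1: reproduce the stated power.** Noncentrality = 1200 / (2000 × √(2/50)) = 1200 / 400 = 3.0. With 98 degrees of freedom the critical value is 1.984, and noncentral t power is 84.4%. The normal approximation gives 85.1%. The stated 84% is reproduced.

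**Step 2: 2000 as the overall SD.** The within-class SD is 2000 × √(1 − R2). With balance within class, the true standard error of the arm difference is 400 × √(1 − R2), but the unstratified test estimates about 400. On the true scale its critical value becomes 1.984 / √(1 − R2).

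- True size of the unadjusted test = P(|t98| > 1.984 / √(1 − R2)).
- Noncentrality = 3.0 / √(1 − R2). Unadjusted power uses the enlarged critical value with 98 df. Adjusted power uses 1.985 with 96 df.

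Worked case, R2 = 0.10: within-class SD = 2000 × √0.90 = 1897; noncentrality = 3.0 / 0.9487 = 3.16; enlarged critical value = 1.984 / 0.9487 = 2.09.

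| R2 (assumed) | True size, unadjusted | Power, unadjusted | Power, adjusted |
|---|---|---|---|
| 0 | 5.0% | 84.4% | 84.4% |
| 0.05 | 4.4% | 85.0% | 86.1% |
| 0.10 | 3.9% | 85.6% | 87.9% |
| 0.20 | 2.9% | 87.0% | 91.3% |

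A simulation of 40,000 trials per setting, with 17, 17 and 16 residents per class in each arm (also an assumption), agrees. For the unadjusted test it gave sizes of 5.1%, 4.6%, 3.8% and 2.9%. The adjusted model stayed between 5.0% and 5.2%.

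**Step 3: what this does to the interval.** The expected 95% half-width of the unadjusted interval is about 1.984 × 400 = 794 steps. Adjusted, it is 1.985 × 400 × √0.90 = 753 steps at R2 = 0.10 and 1.985 × 400 × √0.80 = 710 steps at R2 = 0.20.

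**Step 4: 2000 as the within-class SD.** The overall SD is then 2000 / √(1 − R2), which is 2052, 2108 and 2236 at R2 = 0.05, 0.10 and 0.20. The noncentrality stays at 3.0 and only the enlarged critical value changes. Unadjusted power is 83.1%, 81.7% and 78.2%. Adjusted power stays at 84.4%.

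**The case against.** The strongest reply is that nothing in the protocol says class year affects step counts. No reason is given for the stratification, and another one is visible: the class years are the teams in the second phase, so stratifying splits each team evenly between arms. If class year is unrelated to steps, the unstratified test loses nothing. This stands, and it is why R2 is shown from zero. It does not remove the point, because adjustment costs essentially nothing at R2 = 0 and the protocol cannot rule out a larger value.

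It also stands that the planned t test is valid, since its error is on the conservative side. With an overall SD of 2000, every unadjusted power in the table is at or above the stated 84%, so what is forgone is power beyond the plan. A reader might infer that the 84% is wrong or that the sample is too small. The documents do not support that. Power falls short only if 2000 was meant as a within-class SD, which the text leaves open.

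The balance and class sizes used in the check are assumptions too. Imperfect balance within class would weaken the conservatism.

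A reader might also infer that leaving the choice between two tests open inflates the type I error. Reporting the smaller of the two p-values would do so: simulations with normal data and no class effect gave between 5.5% and 6.4%. But the protocol does not describe that rule. Its wording more naturally means suitability to the distribution, and choosing by a normality pretest gave 5.3% in 4,000 trials, within simulation error of 5%. The selection rule is also something a statistical analysis plan may supply. Nor does the open choice cause the conservatism, which comes only from leaving out the stratification factor.

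**Conclusion.** The mismatch between stratified randomization and an unstratified primary comparison is on the face of the protocol. Its cost depends on R2, which the documents do not give: no power at R2 = 0, about 1 point at 0.05, about 2 at 0.10 and about 4 at 0.20, with true size falling from 5.0% to 2.9% over that range. These figures rest on an overall SD of 2000, 50 per arm, normal data and balance within class. If 2000 is the within-class SD, the unadjusted test falls short of the planned power by roughly 1 to 6 points at R2 from 0.05 to 0.20.

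This is an efficiency improvement that costs almost nothing. It does not invalidate the planned analysis. That the rank sum test does not estimate the mean difference holds whatever R2 is.

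**What to change.** In Statistical methods, replace the randomized-phase comparison with one primary analysis: a linear model of each participant's phase 1 mean daily steps on arm, with class year as a three-level factor, reporting the adjusted mean difference and its 95% confidence interval. Use a class-stratified rank test (van Elteren) as a sensitivity analysis only. In Power analysis, say whether the SD of 2000 is overall or within class year.

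The cost is one or two sentences and two degrees of freedom (96 instead of 98). Class year is already known for every participant. The sample size need not change under either reading of the SD: the adjusted model has at least 84.4% power at every R2 shown.

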### SPECIFIC AIMS

Concisely state the objectives of the study and the hypothesis being tested.

The main objective of this study is to test an intervention to increase the physical activity of medical residents, an employee population with little time for exercise. Specifically, the aims of this study are:

1. To determine if providing medical residents with an activity device that measures steps, distance, and calories burned and tracks this information over time on a website increases residents’ physical activity levels as measured by number of steps per day compared to a control group using a blinded activity device (no feedback).
2. To determine if an unblinded team competition using the activity device directly following the randomized phase increases residents’ activity level compared to baseline.
3. To determine if activity level is associated with change in weight during the residency year.
4. To determine if the average hours of sleep per week is associated with changes in weight and with activity level.

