Team competition phase: Immediately following the randomization phase, all study participants will be unblinded and able to view the Fitbit feedback both on the device and on the website. The control group will be given a password to be able to log on to their personalized Fitbit website. The residents will be divided into 3 teams based on their class: interns, juniors, or seniors. The teams will compete on the average number of steps per week. The team standings will be displayed on the Fitbit website that will be viewed by each study subject. Teams will compete for 6 weeks.

Data to be collected:

Physical assessment*:* All residents who enroll in the Be Fit program will be asked to attend a physical assessment at baseline (between July and November 2010) and at the end (May 2011). All physical assessments will be conducted prior to 10 o’clock in the morning. During these visits, study staff collect weight, height, waist measurements, body fat, blood pressure, and heart rate.

Fasting blood test*:* During each physical assessment, residents enrolled in Be Fit undergo a fasting blood test for lipids. Residents are asked not to have anything to eat or drink after midnight the day before the test.

Survey: All residents enrolled in Be Fit will complete a survey at baseline and at the end of the program. The survey collects information on smoking history, physical activity, and nutritional habits. Age, sex, race/ethnicity, marital status, education level, and care for dependents at home (children, disabled/ill spouse, parent, or child) will be recorded on the survey. The survey also includes a scale that measures psychological stress, called the Schwartz Outcome Scale-10 © (SOS-10 TM). The SOS-10 is a 10 item survey tool to determine a person’s distress level. It is not a diagnostic instrument and cannot be used for making psychiatric diagnoses. The scores range from 0 to 60. Higher scores reflect better psychological health and lower scores indicate emotional distress and lower levels of psychological health. There is a cut off score of 43, and a change of 8 points or greater are a reliable indicator that a person’s psychological status has either improved or deteriorated.

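### The phase 2 versus phase 1 paired test for team competition also picks up about half of any feedback effect, because the control arm first receives feedback when the competition starts

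*Protocol*

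**What the plan says.** All references are to the Protocol.

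- **Specific Aims, aim 2:** "To determine if an unblinded team competition using the activity device directly following the randomized phase increases residents’ activity level compared to baseline".
- **Research Design and Methods, Randomized phase:** for 6 weeks half the participants wear the device with feedback. The other half wear it blinded, with nothing visible on the device or the website.
- **Team competition phase:** once the randomized weeks end, "all study participants will be unblinded and able to view the Fitbit feedback". The 6-week competition between the three residency classes starts at the same point.
- **Study endpoints, primary endpoint:** the second-phase contrast is each participant's change in mean steps from his or her own first-phase level.
- **Statistical methods:** the competition question is assigned to a within-person test: "To determine whether team competition increases activity level, the primary and secondary endpoints from the second phase will be compared" with first-phase results by paired t-tests. No restriction to, or split by, randomized arm is stated. The next sentence adds: "The changes in primary and secondary endpoints during study periods will be compared between the two randomization groups using a two-sample t test". That second test is not tied to the competition question.
- **Power analysis:** 50 per group, a difference of 1200 steps, SD 2000, two-sided 0.05, 84% power. It covers the randomized phase only.

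**The concern.** At the phase change the two arms do not undergo the same change. The arm that already had feedback gains only the competition. The control arm gains the competition and feedback together. A paired comparison over all participants averages these two changes and, under the stated purpose of the test, attributes the average to competition.

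The bias is present whenever feedback works, which is what aim 1 sets out to show. A real feedback effect in phase 1 would thus make a spurious competition finding in phase 2 more likely. At stake is the answer to aim 2, whose comparison is listed under the primary endpoint.

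**Working it through.** **1. The plan's own figure.** Two-sample t-test, 50 per arm, difference 1200, SD 2000: noncentrality = 1200 / (2000 × √(2/50)) = 3.0 on 98 df, giving 84.4% power. The stated 84% is reproduced and not in dispute.

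**2. Expected changes.** Let C be the competition effect and F the feedback effect, with F stable over time and no calendar drift.

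- Feedback arm, phase 2 minus phase 1: C
- Control arm, phase 2 minus phase 1: C + F
- All participants at 1:1 allocation: C + F/2

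With C = 0 and F = 1200 the expected change is +600 steps per day.

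**3. Chance of rejecting when C = 0.** Inputs from the Protocol: 100 participants, SD 2000, two-sided 0.05. The 0.05 is stated for the randomized comparison and is assumed here for the paired test. The correlation ρ between a participant's phase 1 and phase 2 means is not given, so a range is assumed.

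- SD of change within an arm = 2000 × √(2(1 − ρ))
- SD over both arms = √(that SD² + F²/4), because the arm means differ by F
- Noncentrality = (F/2) / (SD over both arms / √100), on 99 df

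Example, ρ = 0.5 and F = 1200: SD of change 2000; over both arms √(2000² + 600²) = 2088; standard error 208.8; noncentrality 600/208.8 = 2.87; rejection 81%.

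The formula is a close approximation. Simulating exactly 50 per arm (200,000 trials per setting) gives the second figure in each cell.

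| ρ | F = 1200: formula / simulated | F = 600: formula / simulated |
|---|---|---|
| 0 | 54% / 54% | 18% / 18% |
| 0.3 | 68% / 69% | 24% / 24% |
| 0.5 | 81% / 82% | 31% / 31% |
| 0.7 | 95% / 96% | 47% / 47% |

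With F = 400 the formula gives 11% to 25% over the same range of ρ.

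**4. Feedback arm alone.** Its expected change is C, so with C = 0 the paired test on 50 participants rejects in 5% of trials whatever F is. This holds only without calendar drift and without growth or fading of the feedback effect.

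**5. The planned between-arm test of changes.** Control change minus feedback-arm change = (C + F) − C = F. If competition acts equally in both arms, C cancels. At F = 1200 this test has 56%, 71%, 84% and 97% power at ρ = 0, 0.3, 0.5 and 0.7, so it may reveal the confounding, but it contains no information on C. Nor is it an independent second estimate of feedback: it reuses the phase 1 data, and if the arms converge in phase 2 it is the phase 1 difference with its sign reversed.

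**6. Precision of the feedback-arm contrast.** With n = 50 and a paired t-test, the difference detectable with 80% power is about 1140 steps at ρ = 0, 810 at 0.5 and 630 at 0.7.

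**The case against.** **Pooling is inferred.** The text never says that the arms are combined, and a SAP that is not shown could present the paired tests by arm. That is fair. But the endpoint refers to each participant, the test carries no arm restriction, and the Protocol itself states the inference to be drawn. If tests by arm were intended, one sentence would settle it.

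**Aim 2 may mean a package.** It speaks of an unblinded team competition against baseline, which can be read as unblinding plus competition in an openly before/after design. This stands in part: the lack of a concurrent control is disclosed and is not itself an error. It does not rescue the test, since half the participants were already unblinded and do not receive that package, and Statistical methods attributes the change to competition.

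**The plan also compares changes between arms.** This would often make the imbalance visible, so a wrong reading is not inevitable. It still does not estimate the competition effect.

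**Stronger readings.** A reader might infer that aim 2 is bound to come out positive. The documents do not support that: 1200 steps is a difference to detect, not an expected effect, and at 600 steps a false positive is less likely than not over the correlations considered. A reader might also infer a family-wise error problem from two comparisons under one primary endpoint. They answer separately stated aims, the 0.05 level is stated only for the randomized phase, and the confounding does not depend on this.

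**Conclusion.** The concern holds as a bias in the competition test. On the natural reading, the all-participant paired change estimates the competition effect plus about half of any feedback effect. With no competition effect, a nominal 5% test rejects in about 54% to 96% of trials if feedback adds 1200 steps, and in about 18% to 47% if it adds 600.

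These figures assume 50 per arm, SD 2000 in both phases, a within-person correlation of 0 to 0.7, a stable feedback effect and no drift. If feedback does nothing, this bias vanishes.

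The fault lies in the match between the phase 2 test and the conclusion attached to it. It should not be read as undermining aim 1: the randomized phase 1 comparison and its 84% power are unaffected.

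**What to change.** In the phase 2 endpoint text and in Statistical methods:

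1. Base the competition contrast on the paired phase 2 minus phase 1 change in the arm that had feedback in both phases.
2. Report the control arm's change separately, labelled feedback plus competition.
3. State that the between-arm difference in change is interpreted neither as a competition effect nor as an independent second estimate of feedback.
4. Word the phase 2 conclusion as an uncontrolled before/after change. Even in the feedback arm it remains open to calendar drift and to growth or fading of the feedback effect.

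A linear week trend should not be the main model; keep it, if at all, as a sensitivity analysis. Over 12 weeks split 6 and 6, phase and week correlate at 1.5 / √(0.25 × 143/12) = 0.87, so the variance of the phase term is inflated by 1/(1 − 0.755), about 4. With independent weekly errors that roughly doubles its standard error.

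The cost is rewording and precision, with no new data. The competition estimate rests on about 50 participants instead of 100, with 80% power for about 630 steps (correlation 0.7) to 1140 steps (correlation 0).

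### The between-arm test on change in SOS-10 and weight is valid, but it leaves the pre-randomization value and the class-year stratum unused and so gives up precision that costs nothing to recover

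*Protocol*

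**What the plan says.** All references are to the Protocol, Research Design and Methods.

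- **Test.** Statistical methods: "The changes in primary and secondary endpoints during study periods will be compared between the two randomization groups using a two-sample t test". No covariate or stratum is mentioned.
- **Outcomes.** The paragraph headed Secondary endpoints opens with "Secondary endpoints will be change in weight during the study period and number of hours of sleep per 24 hour period for each resident". It continues with "Survey data will be used to examine reported changes in physical activity levels, nutritional habits, and sleep habits" and "The survey data will also provide data from the SOS-10 scale on change in psychological stress".
- **Timing.** Under Data to be collected: "All residents enrolled in Be Fit will complete a survey at baseline and at the end of the program". The table under Parameters to be measured dates these visits July–November 2010 and May 2011, and weight is taken at the same two visits. The SOS-10 is part of that survey ("The survey also includes a scale that measures psychological stress") and is scored 0 to 60.
- **Randomization.** "Study participants will be randomized in late December", stratified by class year (intern, junior, senior).

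**The concern.** Both visits bracket the randomization date, so the baseline SOS-10 and baseline weight are true pre-randomization covariates, and they are already being collected. Subtracting the baseline from the May value fixes its coefficient at 1. When the two measurements have equal variance and correlate below 1, the best coefficient is rho, which is less than 1. The change score then over-corrects and carries surplus baseline variation into the outcome.

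This has two consequences for the arm comparison. The confidence interval is wider than the same data allow. In addition, if one arm happens to start lower, regression to the mean will make it appear to improve more. Class year, which the design treats as important enough to stratify on, is also left out of the model.

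The number of participants cannot easily be raised to compensate. There are 170 eligible residents and about 100 are expected to enroll.

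**Working it through.** **Inputs from the Protocol.** 50 per arm and two-sided alpha 0.05 (Power analysis). Baseline before randomization, one follow-up in May 2011.

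**Inputs assumed.** Equal SD at the two times, a baseline-to-May correlation rho shown over a range, and complete baseline–May pairs for 50 per arm. The Protocol gives no SD, effect size, rho or power target for the SOS-10 or weight.

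**Step 1: the plan's own figure.** The standardized difference for steps is 1200/2000 = 0.6. With 50 per arm the noncentral t on 98 df gives 84.4% power (85.1% by normal approximation). The stated 84% reproduces and is not in dispute.

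**Step 2: variance ratio.** In units of SD²:

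- Var(change) = 2(1 − rho)
- Var(residual after baseline adjustment) = 1 − rho² = (1 − rho)(1 + rho)
- Ratio = (1 + rho)/2, below 1 for every rho below 1

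A simulation of 4,000 trials at 50 per arm gave 0.758 at rho 0.5 (theory 0.75) and 0.845 at rho 0.7 (theory 0.85).

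**Step 3: what this means for power.** Take the effect that the change-score t test detects with 80% power at 50 per arm, which is 0.566 SDs of change. This starting point is illustrative and is not a planned figure. Under adjustment the standardized effect becomes 0.566/√((1+rho)/2). At rho 0.5 that is 0.566/0.866 = 0.653. Power is from the noncentral t on 97 df.

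| rho (assumed) | Variance ratio | Equivalent n per arm (50 × ratio) | Power, change score | Power, adjusted |
|---|---|---|---|---|
| 0.4 | 0.70 | 35.0 | 80% | 92% |
| 0.5 | 0.75 | 37.5 | 80% | 90% |
| 0.6 | 0.80 | 40.0 | 80% | 88% |
| 0.7 | 0.85 | 42.5 | 80% | 86% |
| 0.8 | 0.90 | 45.0 | 80% | 84% |
| 0.95 | 0.975 | 48.7 | 80% | 81% |

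Adding two class-year terms leaves 95 df and changes these powers by less than 0.1 point. Simulation of 8,000 trials gave 80.0% against 89.4% at rho 0.5, and 80.1% against 85.7% at rho 0.7.

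**Step 4: chance imbalance.** The standard error of a baseline mean difference is √(2/50) = 0.2 SD. Given a baseline difference b, the expected change-score difference under no effect is −(1 − rho)b.

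| rho | Shift for b = 0.2 SD (1 SE) | Shift for b = 0.4 SD (2 SE) | False-positive rate given b = 0.2 SD | False-positive rate given b = 0.4 SD |
|---|---|---|---|---|
| 0.3 | −0.14 SD | −0.28 SD | 4.6% | 17% |
| 0.5 | −0.10 SD | −0.20 SD | 4.8% | 13% |
| 0.7 | −0.06 SD | −0.12 SD | 5.0% | 10% |
| 0.9 | −0.02 SD | −0.04 SD | 5.0% | 7% |

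A one-standard-error imbalance moves the estimate but leaves the conditional error rate near 5%. The rate rises materially only for larger imbalances.

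**Step 5: overall validity.** Averaged over randomization, the simulated type I error of the change-score test was 4.75% at rho 0.5 and 4.5% at rho 0.7, with mean estimates close to zero.

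**The case against.** **The planned test is legitimate.** A two-sample t test on change is unbiased over randomization, holds its error rate, and has a standard error that already includes chance baseline variation. That stands. A reader might infer from the imbalance argument that the test is biased or invalid. The calculations do not support this: the shift exists only conditionally on an imbalance that has occurred.

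**Coverage is inferred.** Only weight and hours of sleep are named outright as secondary endpoints, and the survey data are introduced more loosely. The test sentence also follows one about comparing the two phases, so it could be read as covering phase-to-phase changes in device data. Part of this stands: for the SOS-10, coverage rests on the paragraph heading. The phase reading does not remove the point, however. Weight change is named outright, the SOS-10 is described as a change, and with only two assessments either change can run only from baseline to May.

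**The gain is smallest where coverage is clearest.** Weight is likely to be highly correlated over time, and at an assumed rho of 0.95 the gain is about 1 point. This stands.

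**Other survey items.** A reader might extend the point to activity, nutrition and sleep scores from the survey. The SOS-10 is the only scored scale the Protocol describes. If the other items are categorical, a linear model suits them no better than a t test.

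**Consequence.** None of the four Specific Aims concerns the SOS-10 or a between-arm survey comparison. By May, the controls have been unblinded and both arms have been through the competition phase. Extra precision on that contrast is therefore unlikely to change a main conclusion, which keeps the point minor.

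**Conclusion.** The point holds as a minor efficiency improvement for secondary outcomes. The Protocol itself names the test, so this is not a detail left to an analysis plan.

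At the assumed correlations of 0.5 to 0.8, adjustment would cut the variance for the SOS-10 by 25% to 10%. That corresponds to 90% down to 84% power where the change score has 80%. For weight the cut is about 2.5% at rho 0.95.

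These sizes rest on equal variances, an undocumented rho, an illustrative 80% starting power and 50 complete pairs per arm. The direction does not depend on the particular rho, as long as it is below 1. Device-measured steps and sleep have no pre-randomization value and are outside the point.

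**What to change.** In Statistical methods, for the between-arm comparison of the SOS-10, replace the two-sample t test on change with a linear model of the May 2011 value on randomized arm, the same participant's baseline value and class year. Report the adjusted arm difference with a 95% CI. Use the same model for weight, expecting little gain. Extend it to other survey items only if they yield a continuous score; categorical items need a model that matches their scale. The analysis of variance across residency years can stay as it is, since those groups are not randomized.

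The cost is about one sentence. No new data, visits or participants are needed, and the three covariate terms (baseline and two for class year) use three degrees of freedom out of about 100 participants. The change does not address the separate fact that the May survey follows unblinding of the control group.
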